## Abstract

**Background:**

Strong evidence exists for the benefits of pulmonary rehabilitation (PR) for people with chronic obstructive pulmonary disease (COPD), however the availability of culturally safe PR for Aboriginal and Torres Strait Islander (Indigenous) Peoples is limited. The study aims to determine whether PR can be implemented within Aboriginal Community Controlled Health Services (ACCHS) to improve outcomes for Indigenous people with COPD.

**Methods:**

Multi-centre cohort study using participatory action research guided by the Knowledge-to-Action Framework. ACCHS supportive of enhancing services for chronic lung disease will be recruited. Aboriginal Health Workers (AHW) and the exercise physiologist (EP) or physiotherapist (PT) within these ACCHS will attend a workshop aimed at increasing knowledge and skills related to management of COPD and the provision of PR. Indigenous people with COPD will be invited to attend an 8-week, twice weekly, supervised PR program. Outcomes: AHW, EP/PT knowledge, skills and confidence in the assessment and management of COPD will be measured before and immediately after the *BE WELL* workshop and at 3, 6 and 12 months using a survey. PR participant measures will be exercise capacity (6-minute walk test (6MWT), health-related quality of life and health status at commencement and completion of an 8-week PR program. Secondary outcomes will include: number, length and cost of hospitalisations for a COPD exacerbation in 12-months prior and 12-months post PR; local contextual factors influencing implementation of PR; specific respiratory services provided by ACCHS to manage COPD prior to project commencement and at project completion. Repeated measures ANOVA will be used to evaluate changes in knowledge and confidence over time of AHWs and EP/PTs. Paired t-tests will be used to evaluate change in patient outcomes from pre- to post-PR. Number of hospital admissions in the 12 months before and after the PR will be compared using unpaired t-tests.

**Discussion:**

Pulmonary rehabilitation is an essential component of best-practice management of COPD and is recommended in COPD guidelines. Indigenous peoples have limited access to culturally safe PR programs. This study will evaluate whether PR can be implemented within ACCHS and improve outcomes for Indigenous people with COPD.

*Trial registration* Australian New Zealand Clinical Trials Registry (ANZCTR) ACTRN12617001337369, Registered 2nd September 2017 https://www.anzctr.org.au/Trial/Registration/TrialReview.aspx?id=373585&isClinicalTrial=False

## Background

Chronic obstructive pulmonary disease (COPD) affects 1.5 million Australians, including 1 in 13 people over 40 years of age [1] with major consequences for participation in work and societal contexts. Aboriginal and Torres Strait Islander Peoples of Australia, hereafter referred to as Indigenous Australians, bear an unequal burden of disease in relation to COPD. Compared to non-Indigenous Australians, the prevalence of COPD is 2.5 times higher, with the death rate being three times higher and the hospitalisation rate five times higher [2]. Importantly, COPD is the greatest contributor to potentially preventable hospitalisations in Indigenous Australians, [3–5] which are those hospitalisations that may have been prevented by provision of evidenced-based interventions delivered in primary care [4].

Pulmonary rehabilitation (PR), a program of exercise training and education, is recommended as best-practice care for people with COPD [6] underpinned by Level 1 evidence from over 85 randomised controlled trials in two Cochrane reviews [7, 8]. These reviews concluded that pulmonary rehabilitation improves exercise capacity, reduces symptoms of breathlessness and fatigue, improves health-related quality of life, and reduces hospital admissions and mortality in people with COPD [7, 8]. Reducing hospitalisations is not only important for reducing health care costs, but a valuable outcome for Indigenous people since hospitalisations cause dislocation from family, especially if hospitals are distant from the communities in which they live. Reducing mortality from COPD is also vital in addressing the gap in life expectancy experienced by Indigenous compared to non-Indigenous Australians [2].

In Indigenous Australian communities there have been coordinated approaches to improve the management of other chronic diseases such as diabetes, cardiovascular and renal disease, however efforts to improve the management of chronic lung diseases, such as COPD, have been inadequate and inconsistent. A major reason for limited access to best-practice management of COPD is the perception by Indigenous peoples that PR programs offered in centre-based hospital outpatient departments are unwelcoming or culturally unsafe [9] due to racism [10]. Additionally there is a lack of knowledge, skills and confidence of healthcare professionals, as well as lack of funding, to implement PR programs in rural and remote Australia [11], including within Aboriginal Community Controlled Health Services (ACCHS). This means that Indigenous peoples with COPD are much less likely to receive best-practice management for COPD and more likely to have poorer health outcomes.

A recent systematic review of PR for Indigenous peoples with COPD in Australia, Canada, New Zealand and the United States of America found only one published study reporting the outcomes of PR, [12] highlighting the paucity of data evaluating PR in Indigenous communities.

## Aim and objectives

The broad aim of the *Breathe Easy Walk Easy, Lungs for Life (BE WELL)* project is to evaluate the implementation of lung health services within ACCHS, particularly the provision of PR.

The implementation objectives (1–3 in the list below) and the intervention objective (4 in the list below) of the study are to:Evaluate the ability of the *BE WELL* program to enhance the knowledge, skills and confidence of Aboriginal Health Workers in the assessment and management of people with COPD and in the delivery of a culturally safe PR program that includes exercise training and patient education.Identify the structural, systems and other contextual factors that influence successful implementation and sustainability of PR programs within ACCHS.Determine the uptake of respiratory assessment and PR programs by ACCHSDetermine the impact of the *BE WELL* PR program on health outcomes and health care utilisation and costs (particularly hospitalisations) of Indigenous people with COPD.

## Methods/design

The study will be a cohort study using implementation science and participatory action research methods guided by the Knowledge-to-Action Framework [13–15]. This will be an iterative process of reflection and action carried out with and by ACCHS rather than ‘on’ them [15]. Fig. 1 maps the knowledge already established for PR and the elements of the *BE WELL* program in the Knowledge-to-Action Framework. The study has ethics approval from the Aboriginal Health and Medical Research Council of New South Wales, Australia (Project 1261/17). All participants will provide written, informed consent. Any protocol amendments will be approved by the ethics committee and reported on the Australian New Zealand Clinical Trials Registry.

**Fig. 1 Fig1:**
[figure not shown]
Knowledge-to-Action Framework. *ACCHS* Aboriginal community controlled health service; *COPD* Chronic obstructive pulmonary disease; *COPD-X* Australian COPD guidelines; *PR* Pulmonary rehabilitation

## Participants

ACCHS in New South Wales, Australia will be invited to participate in the study with the aim of recruiting one ACCHS from each of the following regions: metropolitan, regional, rural, remote. These regions will be identified by the remoteness classification [16]. Initial engagement of ACCHS will be facilitated by the Poche Centre for Indigenous Health, University of Sydney.

Within the ACCHS the following participants will be recruited: (1) ACCHS management who have oversight or involvement in managing any aspects of the *BE WELL* project; (2) Aboriginal health workers (AHWs) who are nominated by the ACCHS to work within the local *BE WELL* team to develop and aid provision of a PR program; (3) Exercise physiologists (EP) or physiotherapists (PT) who are contracted by the ACCHS to provide the PR program within the ACCHS; (4) Aboriginal people attending the ACCHS who have a confirmed diagnosis of COPD by spirometry [ratio of forced expiratory volume in one second (FEV_1_) to forced vital capacity (FVC) of less than < 0.7] and who are referred to the *BE WELL* PR program.


The intervention will consist of provision of a PR program run by EP/PT and AHWs. Participants with COPD will be asked to attend twice a week for eight weeks. The PR program will consist of patient assessment, exercise prescription and training, patient education, and patient reassessment at program completion as outlined below.*Patient Assessment* will include medical history; lung function testing using spirometry (MIR Spirodoc Spirometer, Rome, Italy); evaluation of exercise capacity using the six-minute walk test (6MWT) performed twice and using standard procedures [23] including measurement of oxygen saturation and pulse rate each minute using a pulse oximeter (Spirodoc); evaluation of health-related quality of life using the St George’s Respiratory Questionnaire (SGRQ) [24] and the EuroQual-5D-5L questionnaire (EQ5D5L) [25]; health status using the COPD Assessment Test (CAT) [26]. Each ACCHS will be provided with equipment needed to perform patient assessment and monitoring during pulmonary rehabilitation, including a spirometer combined with a pulse oximeter (Spirodoc).*Exercise prescription and training* will include walking, stationary cycling and resistance training. Walking training intensity will be based on walking at 80% of the better 6MWT speed and will either be walking on a flat indoor track or on a treadmill. Cycle training intensity will be 60% of peak work rate calculated from the 6MWT [27]. Participants will start with 10 min walking and 10 min cycling which will be progressed to 20 min walking and 20 min cycling over the first 3 weeks of the program. Intensity will be progressed by increasing walking speed on the treadmill or indoor track and work rate (watts) on the cycle ergometer to keep the symptom scores of dyspnoea or perceived exertion (whichever is the highest) at 3–4 (‘moderate' to ‘somewhat severe’) on the 0–10 category-ratio scale [28]. Resistance training will use elastic resistance bands and simple hand weights for upper limbs and body weight exercises such as squats, sit-to-stand, step-ups for lower limbs. To ensure equity of equipment, each ACCHS will be provided with a treadmill, cycle ergometer and elastic resistance bands. Prior to starting the PR program, participants will be assessed by a general medical practitioner to optimise medications and to ensure that there are no contraindications to exercise training.*Patient education* ‘yarning’ sessions’, led by the AHW, will occur once a week at the end of one of the exercise sessions. There will be seven topics for patient education (see point 3 above).*Patient reassessment* at the end of the PR program will use the 6MWT, SGRQ, CAT and EQ5D-5L. Spirometry will also be performed to determine whether the participant’s lung function remained stable during the pulmonary rehabilitation program. Participants will also be asked to complete a survey of their experience of pulmonary rehabilitation (Table1).

**Table 1 Tab1:** Study objectives and outcome measures

Objectives	Outcome measure	Purpose	Description	Participants	When administered
*Implementation*					
Objective 1: Enhance health provider knowledge, skills and confidence	*BE WELL* Health Provider Impact Questionnaire	To evaluate the effects of the *BE WELL* workshop on health care provider knowledge, confidence and skills	The questionnaire will include a Likert scale to assess self-reported knowledge of COPD, and skills in assessing people with COPD (including spirometry and 6MWT), and confidence in exercise prescription (EP/PTs only) and providing an exercise program and education for Indigenous people with COPD	AHWs and EPs/PTs who attend the *BE WELL* workshop	Before and immediately after the *BE WELL* workshop, and at 3, 6 and 12 months post-workshop
	Online education survey	To evaluate the AHW and EP/PT experience of the online education sessions for developing ‘yarning’ educational resources for *BE WELL* participants undertaking the PR program	A 15-question survey using a 5-point Likert scale evaluating the mode of delivery, structure of the sessions, and engagement	AHWs and EPs/PTs who attend the *BE WELL* online education sessions	After completion of the online education sessions at each participating ACCHS
	Online education semi-structured interviews	To explore the AHW and EP/PT experiences of the online education sessions to completement the responses from the online education survey	To guide discussion, 13 interview questions covering context, co-design, engagement, knowledge and understanding, cultural integration and impact will be used. The interviews will be conducted by a member of the research team experienced in qualitative interviews and who is not involved in the delivery of the online education sessions	AHWs and EPs/PTs who attend the *BE WELL* online education sessions	After completion of the online education sessions at each participating ACCHS
Objective 2: Identify factors that influence successful implementation	Focus groups	To explore the local structural, system level and other contextual factors that could influence successful implementation within each ACCHS	To guide discussion there will be questions relating to the elements of the RE-AIM framework i.e. Reach, Effectiveness, Adoption, Implementation, Maintenance	ACCHS staff involved in *BE WELL* project	At project inception and at 12-months after the *BE WELL* workshop
	Survey	To gain feedback from patients about the *BE WELL* PR program	Survey using 5-point Likert scale to evaluate patients’ knowledge of lung disease, confidence in self-management, program satisfaction and suggestions for improvement	Indigenous patients enrolled in the *BE WELL* PR program	At the completion of each patient’s PR program
	Focus groups	To gain a more in-depth understanding of the patient experience of the *BE WELL* PR program	To guide discussion there will be questions relating to patients’ experiences of the *BE WELL* PR program and patients’ perceived changes in knowledge of lung disease, confidence in self-management, and their degree of satisfaction with the program. Advice will be sought from each ACCHS to determine the most culturally appropriate method of engaging with patients	Indigenous patients enrolled in the *BE WELL* PR program	After completion of PR by a group of participants
Objective 3: Uptake of new services for COPD management	*BE WELL* Service Delivery Inventory	To evaluate the extent of respiratory services at each ACCHS and the impact of the *BE WELL* program on the services provided	The inventory will cover the following services: spirometry for assessment of COPD, assessment of smoking status, provision of evidence-based smoking cessation advice and/or treatment, provision of pulmonary rehabilitation programs that include exercise training and patient education	Executive staff of each ACCHS	At initial consultation and at project completion
*Intervention*					
Objective 4: Impact of *BE WELL* PR program on patient outcomes and health care costs	6MWT (23)	To evaluate functional exercise capacity	Measures distance walked in 6 min on a flat, indoor track. Two tests will be performed at baseline and one test at program completion. Oxygen saturation and pulse rate will be recorded continuously using a pulse oximeter (MIR Spirodoc Spirometer, Rome, Italy)	Indigenous patients attending the *BE WELL* PR program	Before and after participation in the 8-week *BE WELL* PR program
	SGRQ (24)	To evaluate HRQoL	A 50-item questionnaire with domains of impact, symptoms and activity impairment associated with COPD		
	EQ5D-5L (25)	To evaluate HRQoL	A generic quality of life questionnaire consisting of five dimensions (mobility, self-care, usual activities, pain/discomfort, anxiety/depression) which will be used in cost-effectiveness analysis		
	CAT (26)	To evaluate the impact that COPD on wellbeing and daily life	An 8-item questionnaire evaluating symptoms, activity limitations, sleep, confidence		
	Hospitalisations	To evaluate the impact of the *BE WELL* PR program on hospitalisations	Hospital separation data will be collected from the NSW Centre for Health Record Linkage (CHeReL). Administrative hospital records including information on the Diagnostic Related Group (DRG) classification and International Classification of Disease (ICD-10) codes for hospital separations will be used to estimate a cost using local cost weights	Indigenous patients who participated in the *BE WELL* PR program	In the periods 12 months preceding and following participation in the *BE WELL* PR program
	Other healthcare costs (GP visits, medications)	To evaluate the impact of the *BE WELL* PR program on other healthcare costs	Costs of medical services and medications will be recorded from patients who consent to access of their administrative health care use data through the Medical and Pharmaceutical Benefits Schedules (PBS) from Medicare Australia. Additional primary health care and medication use data will be abstracted from primary health care histories particularly in sites where the PBS have limited implementation, e.g. very remote Australian health care services		
	Costs of *BE WELL* pulmonary rehabilitation program	To determine the costs of provision of the *BE WELL* PR program for comparison with any costs savings	Costs of program delivery will include staff time, facility costs, training resources	Executive staff of the ACCHS	During the *BE WELL* project

*ACCHS* Aboriginal community controlled health services, *AHW* Aboriginal health worker, *BE WELL* Breathe easy walk easy lungs for life, *CAT* COPD assessment test, *COPD* Chronic obstructive pulmonary disease, *EP/PT* Exercise physiologist/physiotherapist, *EQ5D-5L* EuroQual 5 dimensions-5 levels, *GP* General practitioner, *HRQoL* Health-related quality of life, *PR* Pulmonary rehabilitation, *SGRQ* St George’s respiratory questionnaire, *6MWT* Six-minute walk test

## Outcome measures

The *BE WELL* program will be evaluated using the RE-AIM Framework of Reach, Effectiveness, Adoption, Implementation and Maintenance [29] as well as patient experience of PR and ACCHS experience of implementing PR. For RE-AIM, Reach will be assessed by the number of participants with COPD who attend the *BE WELL* program in relation to the number of people with COPD being managed by each participating ACCHS. Effectiveness will be assessed by the outcomes of participants in response to the *BE WELL* PR program, particularly improvements in exercise capacity and health-related quality of life. Adoption will be assessed by the uptake of the *BE WELL* PR program by patients with COPD and by the AHWs involved in the delivery of the program. The barriers and facilitators to adoption by people with COPD and AHWs will be reported. Implementation will be assessed by determining whether the *BE WELL* PR program was provided as intended. Maintenance will be determined by the number of ACCHS that continue to offer the *BE WELL* PR program at completion of the project. The intervention outcomes will be measured by the objective assessments of the participants before and at completion of the *BE WELL* PR program. The outcome measures specifically related to the main study objectives and the timing of these measures are detailed in Table 1.

## Reference group

A *BE WELL* Reference Group will be established at the commencement of the project. The Reference Group will consist of representatives from Aboriginal communities and organisations, and from relevant State and Federal health care and professional bodies. This group will provide expertise and guidance throughout the project, will ensure that the project initiatives fit with the organisational, policy and cultural context, and will advise on strategies to enable sustainable implementation and transferability to the broader ACCHS sector.

## Data and data analysis

Plans for data entry, coding, security, and storage will be held on the secure Research Management Dashboard of the University of Sydney. Quantitative data will be collated and analysed using SPSS statistics package. Scores from the *BE WELL Health Provider Impact Questionnaire* before and immediately after the workshop will be compared using paired t-tests. Repeated measure ANOVA will be used to evaluate knowledge retention over time. For categorical measures of self-rated knowledge, confidence and skills, change scores will be calculated and analysed using Wilcoxon’s signed ranks test. Patient outcomes for exercise capacity and health-related quality of life will be compared before and after PR using paired t-tests. The number of hospital admissions for respiratory related care in the 12 months before and after the *BE WELL* PR program will be compared using unpaired t-tests and the number of patients admitted before and after program will compared using proportions. The costs of delivery of the *BE WELL* program will be determined and potential savings against reductions in health care utilisation will be quantified [30]. For qualitative data, the focus groups with ACCHS staff and with participants in the *BE WELL* PR program and interviews with AHW who participate in the online education sessions will be digitally recorded and transcribed. Data will be analysed in QSR International NVivo using inductive coding and thematic analysis [31]. Any adverse events will be reported immediately to the ethics committee and will be reported in any publications.

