## Sample size

Sample sizes have been calculated for the quantitative measurements. For evaluating changes in health worker knowledge of COPD management, the scores from the objective knowledge test in *BE WELL Health Provider Impact Questionnaire* will be used. The sample size, based on pilot data demonstrating change in knowledge score of 7 marks [standard deviation (SD) 4.5] [32], requires eight AHW participants, with a power of 80%, alpha 0.05, allowing for a 20% dropout (i.e. two AHWs per ACCHS). For the patient outcomes, based on our pilot study in rural and remote areas, to detect a change in 6MWT of 48 m, SD 70 m [11], with a power of 80% and alpha 0.05, 40 patients will be required, allowing for a 15% dropout. For quality of life, to detect a minus 4-point improvement in SGRQ (which is the minimal important difference [33]) with SD 6 points, 42 patients will be required, allowing for a 15% dropout, with power 80% and alpha 0.05. For hospitalisations, we have conservatively assumed a 20% reduction in hospital admissions. Therefore 97 patients would be needed, power 80%, alpha 0.05, allowing for 15% drop-out. Based on the largest patient sample size required, 97 patients with COPD will be recruited. For qualitative data, focus groups and interviews will be undertaken with participants until no new information is obtained and saturation is achieved.

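### Knowledge retention is assigned to a repeated-measures ANOVA with no stated surveys or comparison; over all five surveys the overall time test cannot separate knowledge kept from knowledge lost

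*Protocol article*

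**What the plan says.** Table 1 of the protocol article schedules the health provider questionnaire at five times: "Before and immediately after the *BE WELL* workshop, and at 3, 6 and 12 months post-workshop". It goes to both AHWs and EPs/PTs.

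The section *Data and data analysis* splits the knowledge analysis in two. For the immediate effect, scores "before and immediately after the workshop will be compared using paired t-tests". For what follows, "Repeated measure ANOVA will be used to evaluate knowledge retention over time". The abstract describes the ANOVA more broadly: "Repeated measures ANOVA will be used to evaluate changes in knowledge and confidence over time of AHWs and EP/PTs". Categorical self-ratings are handled separately, by Wilcoxon signed-rank tests of change scores.

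The section *Sample size* rests on pilot data with a mean change in knowledge score of 7 marks and an SD of 4.5. It arrives at eight AHWs at 80% power and alpha 0.05, including 20% dropout.

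The article does not say whether the pre-workshop survey enters the ANOVA. It names no reference survey, contrast or criterion for retention.

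**The concern.** Retention asks whether the marks gained at the workshop are still there at 3, 6 and 12 months. The null hypothesis of a one-way repeated-measures ANOVA is that the mean is the same at every survey entered. With the pre-workshop survey included, the workshop gain alone makes that null false, whatever happens later. A significant result then repeats, in less specific form, what the paired t-test has already shown.

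With the pre-workshop survey left out, the meaning reverses. A significant result now points to change after the workshop, and a non-significant one might be taken as retention. With six to eight people, non-significance is weak evidence of that.

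The two readings therefore give opposite meanings to the same p-value, and the article does not say which applies. At stake is the interpretation of the 3-, 6- and 12-month knowledge scores under Objective 1.

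**Working it through.** **Inputs.** From *Sample size*: gain 7 marks, SD 4.5 (read as the SD of the change), 8 AHWs, 20% dropout, alpha 0.05 (two-sided assumed). From Table 1: five surveys. Assumed, because the article gives no covariance: the SD of any pairwise difference is 4.5 with equal correlation, so the ANOVA error variance is 4.5²/2 = 10.125.

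**1. The plan's own figure.** Standardised change d = 7/4.5 = 1.556. Power of the paired t-test (exact noncentral t) is 74.0% at n=5 and 85.7% at n=6, so 6 completers are needed. 6/0.8 = 7.5, rounded up to 8. The plan's eight is reproduced, and it implies about six completers after dropout.

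**2. ANOVA on all five surveys.** Noncentrality λ = n × Σ(μ − mean)²/10.125, with df (4, 4(n − 1)).

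- Fully kept, means 0, 7, 7, 7, 7: grand mean 5.6; sum of squares 5.6² + 4 × 1.4² = 39.2.
- Fully lost by 3 months, means 0, 7, 0, 0, 0: grand mean 1.4; sum of squares 5.6² + 4 × 1.4² = 39.2.

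The two sums are identical, so λ is identical: 8 × 39.2/10.125 = 30.97 at n=8 and 23.23 at n=6.

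| Scenario | n=8 | n=6 |
|---|---|---|
| Fully kept | 99.2% | 94.7% |
| Fully lost by 3 months | 99.2% | 94.7% |
| Even decline to zero by 12 months | 98.8% | 93.3% |
| Fully kept or lost by 3 months, Greenhouse-Geisser (simulated) | about 98% | about 86% |

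As a check on the covariance assumption, simulation under AR(1) with correlation 0.5, uncorrected, gives 94% (kept) against 96% (lost by 3 months) at n=8, and 82% against 85% at n=6. The level moves; the inability to separate the cases does not.

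**3. ANOVA on the four post-workshop surveys.** Same formula, df (3, 3(n − 1)).

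- Fully kept: all means equal, so rejection is 5%.
- Even decline to zero (7, 4.67, 2.33, 0): sum of squares 27.22; λ = 21.51 and 16.13; power 96% at n=8 and 85% at n=6.
- Even loss of half the gain (7, 5.83, 4.67, 3.5): sum of squares 6.81; λ = 5.38 and 4.03; power 40% and 29%. Missed: 60% and 71%.

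**4. Planned contrasts.** Paired t with SD 4.5.

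- 12 months minus pre-workshop, gain fully kept: power 96% at n=8 and 86% at n=6; 5% if fully lost.
- 12 months minus immediately post-workshop, half the gain lost (3.5 marks): power 48% at n=8 and 34% at n=6.
- 95% CI half-width, t × 4.5/√n: 2.365 × 4.5/√8 = 3.8 marks; 2.571 × 4.5/√6 = 4.7 marks.

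**The case against.** The article does not say that the overall p-value will decide retention. Follow-up comparisons after an ANOVA are commonly left to an analysis plan, which is not shown here. That stands: a reader might infer that retention will be judged on the overall time effect alone, but the document does not commit to that. What remains is that the article names a test for a specific question, and that test's overall result does not answer it on the reading the abstract fits.

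A reader might also infer that neither version of the ANOVA bears on retention. That goes too far. The immediate gain has its own paired t-test, so an ANOVA on the four post-workshop surveys is a possible reading, and it does separate full retention (5%) from an even decline to zero (96% at n=8, 85% at n=6). Its limit is narrower: it cannot support a positive claim of retention.

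Nor is 99% an unconditional figure. It needs eight completers, equal correlation and no sphericity correction. It could rise if EPs/PTs are pooled with AHWs, whose combined number is not given.

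Finally, low power against a partial loss is a sample-size matter that contrasts barely cure: 48% and 34% for a half loss, against 40% and 29% for the four-survey ANOVA. That also stands. And Objective 1 speaks of enhancing knowledge, skills and confidence, not of lasting change; the retention question comes from the analysis section itself and from the 12-month survey schedule.

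**Conclusion.** The point holds in conditional form. The article gives retention to a repeated-measures ANOVA without fixing which surveys enter or what comparison counts as retention. Over five surveys, the overall time effect is about as likely to be significant when all knowledge is kept as when all is lost: about 99% with 8 completers, about 95% with 6, and about 86% with 6 under Greenhouse-Geisser. Over four surveys, complete loss is usually detected, but a loss of half the gain is missed about 60% to 71% of the time, so non-significance is not evidence of retention.

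The percentages rest on the pilot gain and SD, an assumed equal correlation and complete data. The equality of the kept and lost-by-3-months cases over five surveys holds at any sample size and for any gain under equal correlation, and nearly holds under the AR(1) alternative. The article does not show that the investigators will misread the result; it leaves the reading open where two opposite interpretations are possible.

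**What to change.** State in *Data and data analysis* which surveys enter the ANOVA, and keep it, if wanted, as an overall test only. Base retention on two planned contrasts, each with a 95% CI:

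1. 12 months minus pre-workshop: is knowledge still above its starting level?
2. 12 months minus immediately post-workshop: how much of the gain has gone?

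The 3- and 6-month surveys can be treated the same way as secondary contrasts. Add that a non-significant ANOVA or contrast will not be reported as retention.

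The cost is wording only: no new data, surveys or participants. The drawback is that imprecision becomes visible. A CI half-width of 3.8 to 4.7 marks exceeds half of the 7-mark gain, so the second contrast will often be inconclusive about a partial loss. What is gained is an estimate that can be read directly, not much extra power.
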